**Methods:**

This study adopts a randomized controlled trial design, with participants randomly assigned to either a control group or a Liuzijue group. The control group receives standardized pharmacological treatment, while the Liuzijue group receives the same pharmacological treatment combined with Liuzijue intervention. The coprimary outcome measures are the 6-minute walk test and surface electromyography of the respiratory muscles. Secondary outcome measures include pulmonary function tests and respiratory questionnaires. Exploratory outcome measures include isokinetic strength testing of the core muscle groups and kinematic analysis.

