### Primary Outcome Measures

#### Overview

The primary outcomes of this trial are surface electromyography (sEMG) and 6MWT.

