#### sEMG

sEMG is a noninvasive technique that allows real-time and precise assessment of the electrical activity of superficial muscles, thereby providing an objective reflection of muscle recruitment and functional status. Previous studies [41,42] have demonstrated a high correlation between sEMG and invasive electromyography (EMG) signals, while effectively avoiding the stress responses induced by traditional invasive methods, which facilitates the acquisition of more reliable experimental data.

In this study, a 16-channel NORAXON Wireless EMG system (NORAXON Wireless EMG) combined with EMGworks Acquisition 4.5 (Delsys) software will be used to noninvasively evaluate changes in respiratory muscle strength in patients with COPD before and after the intervention. The primary parameters measured will include the root mean square of the EMG signal, averaged EMG, and mean power frequency. Root mean square and averaged EMG are used to quantify the intensity of muscle activation, while mean power frequency is used to assess muscle fatigue [43]. The muscles monitored include the sternocleidomastoid, trapezius, intercostal muscles, diaphragm, rectus abdominis, external oblique, internal oblique, transversus abdominis, and multifidus. Electrode placement strictly follows the SENIAM (Surface Electromyography for the Non-Invasive Assessment of Muscles) protocol, with recommended locations for respiratory muscles summarized in Table 3 [43-47]. Before signal acquisition, the skin will be thoroughly cleansed with alcohol to reduce impedance and ensure high-quality data.

**Table 3. T3:** Electrode placement locations for respiratory muscles based on the SENIAM^a^ protocol.

No.	Muscle	Electrode placement
1	Sternocleidomastoid	The midpoint of the prominently bulging muscle on the anterolateral neck when the head is turned to the opposite side
2	Trapezius	The midpoint between C7^b^ and the acromion
3	Intercostal muscles	Two finger-breadths lateral to the sternum, at the midpoint between the second and third ribs
4	Diaphragm	The intersection of the midclavicular line and the 8th rib
5	Rectus abdominis	Two finger-breadths lateral to the umbilicus
6	External oblique	The intersection of the anterior axillary line and the 10th rib
7	Internal oblique	Located 2 cm superior to the ASIS^c^
8	Transversus abdominis	2 cm medial to the ASIS, slightly below the horizontal line of the umbilicus

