9	Multifidus	The junction between the middle $\frac{1}{3}$ and medial $\frac{1}{3}$ of the line from PSIS^d^ to L5^e^

a SENIAM: Surface Electromyography for the Non-Invasive Assessment of Muscles.

b C7: the seventh cervical vertebra.

c ASIS: anterior superior iliac spine.

d PSIS: posterior superior iliac spine.

e L5: the fifth lumbar vertebra.

The sEMG assessment will consist of static and dynamic tests. In the static test, participants will stand quietly while EMG signals are recorded for 5 seconds at rest, at the end of maximal inspiration, and at the end of maximal expiration, with each condition repeated three times at two-minute intervals. The dynamic test will involve a 10-meter walking trial, during which participants are instructed to walk as fast as possible along a corridor while both walking time and EMG signals are recorded simultaneously. The electrode placement for sEMG is illustrated in Figure 3. The sEMG data will be collected in week 0 and week 13.

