### Secondary Outcome Measures

#### Overview

The secondary outcomes of this trial include PFT, St. George’s Respiratory Questionnaire (SGRQ) and isokinetic muscle strength test (IKMT) of the core muscle group.

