### Statistical Analysis

Statistical analyses will be executed using SPSS (version 27.0), adhering to a two-sided significance threshold of *P*<.05 while reporting effect sizes and 95% CIs where appropriate. Baseline characteristics will be summarized solely through descriptive statistics without formal hypothesis testing, with continuous variables first evaluated for normality and homogeneity of variance to determine their presentation as either mean with SD or median with IQR.

Under an intention-to-treat framework encompassing all randomized participants, missing data patterns will be evaluated and addressed via multiple imputations, the robustness of which will be subsequently verified through sensitivity analyses including per-protocol and complete-case approaches. Primary outcomes will be modeled using linear mixed-effects specifications that will incorporate group, time, and their interaction as fixed effects alongside participant-level random intercepts to account for the repeated-measures design.

For continuous secondary outcomes, analysis of covariance adjusted for baseline values will be used where appropriate, whereas other continuous and categorical variables—the latter summarized as frequencies and percentages—will be scrutinized using parametric, nonparametric, chi-square, or Fisher exact tests depending on data distribution, with false discovery rate adjustments applied throughout to mitigate type I error inflation from multiple comparisons.

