## Discussion

### Principal Findings

This study is expected to demonstrate that Liuzijue can improve respiratory muscle function, leading to enhanced exercise capacity and health-related quality of life in patients with stable COPD.

As the third leading cause of death worldwide, COPD profoundly impairs patients’ exercise capacity and quality of life, while imposing a substantial burden on health care systems and socioeconomic resources [3,4]. Despite the availability of various pharmacological and nonpharmacological interventions, the overall control rate of COPD remains unsatisfactory, particularly in the domain of rehabilitation during the stable phase. This highlights the need for effective rehabilitation strategies targeting both functional capacity and respiratory muscle performance.

A growing body of evidence indicates that traditional Chinese exercise therapies can significantly improve the exercise capacity and quality of life in patients with stable COPD and have been incorporated into pulmonary rehabilitation programs [64]. However, current research on Liuzijue remains limited, with a lack of mechanistic studies from the perspective of respiratory muscle function changes.

In line with this aim, the discussion is organized around functional outcomes, mechanistic evidence, and clinical implications. To systematically evaluate changes in symptoms and functional outcomes in patients with COPD before and after the intervention, this study will use three well-established and widely used outcome measures, including PFT, the 6MWT, and the SGRQ, with the 6MWT designated as the primary outcome. As a core indicator reflecting overall exercise capacity and functional performance, the 6MWT is particularly sensitive in capturing changes in daily physical activity levels among patients with COPD and is therefore selected as the primary endpoint of this study [48,49]. PFTs will be used to objectively assess the physiological status of respiratory function [50], while the SGRQ will comprehensively reflect symptom burden and health-related quality of life from the patient’s subjective perspective [53,54]. Collectively, these measures establish a comprehensive outcome evaluation framework encompassing physiological, functional, and patient-reported dimensions, in accordance with the requirements of high-quality clinical research for scientific rigor, comparability, and clinical relevance of primary and secondary outcomes.

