Building upon this framework, this study further integrates static and dynamic sEMG together with IKMT to objectively characterize the functional properties of respiratory and core muscle groups. This approach aims to address a key limitation of previous COPD rehabilitation studies, in which the mechanisms underlying intervention effects—particularly those related to respiratory muscle function—have received relatively limited attention. Specifically, sEMG, as another primary outcome measure, can objectively and clearly reflect changes in respiratory muscle function in participants. In this study, both static and dynamic sEMG assessments will be performed to comprehensively evaluate respiratory muscle activation patterns under different conditions. Static sEMG will be applied to analyze muscle excitability and recruitment patterns of respiratory muscles at rest, whereas dynamic sEMG will be used to record muscle activation during movement [41-43]. Combined with IKMT of the core musculature, these assessments will enable quantitative evaluation of the strength and endurance of accessory respiratory muscles [57]. Through comprehensive multimodal analysis, the functional status and adaptive changes of respiration-related muscle groups can be more thoroughly elucidated, providing objective and reliable evidence for evaluating the mechanistic effects and long-term value of Liuzijue interventions.

In addition, a novel kinematic perspective will be introduced by incorporating gait analysis and plantar pressure assessment to systematically evaluate changes in lower-limb function. This strategy will help exclude potential confounding effects arising from muscular adaptations outside the respiratory system, thereby further strengthening the accuracy and internal validity of intervention effect determination [62,63].

The two coprimary outcomes in this study will serve distinct yet complementary purposes. The 6MWT is selected to capture clinically meaningful changes in functional exercise capacity, whereas sEMG provides a more direct assessment of neuromuscular activity in the respiratory muscles, thereby offering mechanistic insight into the intervention’s effects. Regarding sample size estimation, we based our calculations on the 6MWT, primarily because published data on sEMG responses to Liuzijue training in patients with COPD remain limited, precluding a reliable a priori estimate.

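### sEMG is co-primary but not reduced to one testable endpoint or tied to a success rule, and the sample size covers a single 6MWT test, so the stated alpha and power do not describe the co-primary claim

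*Protocol article*

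**What the plan says.** Primary Outcome Measures, Overview, gives two primary outcomes: "The primary outcomes of this trial are surface electromyography (sEMG) and 6MWT". The Abstract and the Discussion call them coprimary.

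The sEMG section then lists what is measured: "The primary parameters measured will include the root mean square of the EMG signal, averaged EMG, and mean power frequency". It names nine muscles. For the static test, "EMG signals are recorded for 5 seconds at rest, at the end of maximal inspiration, and at the end of maximal expiration"; a fast 10-metre walk is the dynamic test. The article does not single out a muscle, parameter or condition, define a composite, or give a direction of benefit.

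The Discussion (Principal Findings) is not consistent. One paragraph describes the outcome set "with the 6MWT designated as the primary outcome" and goes on to call the 6MWT the primary endpoint. The following text calls sEMG another primary outcome measure.

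Sample Size Calculation uses the 6MWT alone: two-sided alpha .05, 80% power, difference 54 m, SD 80 m, giving 32 per group, raised to 38 for 15% dropout. The Discussion explains why sEMG was not sized: "published data on sEMG responses to Liuzijue training in patients with COPD remain limited, precluding a reliable a priori estimate".

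Statistical Analysis models the primary outcomes with linear mixed models. Its next paragraph, on secondary and other variables, ends "with false discovery rate adjustments applied throughout to mitigate type I error inflation from multiple comparisons". The family is not defined.

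**The concern.** An alpha and a power belong to a decision rule. Here the rule is missing and one of the two primary domains is a set of measurements, not an endpoint. The only test for which error rate and power were considered is the 6MWT test, yet the trial's main question, respiratory muscle function, is carried by sEMG.

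If one favourable sEMG result is enough, the analyst can choose among many after seeing the data, and a claim about respiratory muscle function would carry a false-positive risk well above .05. If both domains must succeed, the chance of a positive trial is lower than the 80% that readers will take from the sample-size section. Neither consequence is visible in the article.

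**Working it through.** **Number of sEMG variables.** Inputs from the sEMG section: 3 parameters, 9 muscles, 4 conditions (rest, maximal inspiration, maximal expiration, walk).
- Fully crossed: 3 × 9 × 4 = 108.
- Static only: 3 × 9 × 3 = 81.
- One condition: 3 × 9 = 27.

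The text implies the crossing but does not state it, so 108 is an upper figure.

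**The plan's own sample size.** n = (1.960 + 0.842)² × 2 × 80² / 54² = 34.45, so 35 per group, not the stated 32. This is a separate fault, noted because it sets the baseline. With 32 evaluable per group the standardised shift is 54 / (80 × √(2/32)) = 2.70. 6MWT power at .05 is then 0.770 (normal) or 0.757 (t), before any multiplicity.

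**Either domain suffices, each test at .05, no adjustment.** One sEMG variable plus 6MWT, independent: 1 − 0.95² = 0.0975. For at least one false positive among k sEMG variables, independence gives 1 − 0.95^k. Correlated cases were simulated with an assumed equal correlation:

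| Correlation (assumed) | 27 variables | 108 variables |
|---|---|---|
| 0 | 0.75 | 0.996 |
| 0.3 | 0.63 | 0.95 |
| 0.5 | 0.48 | 0.79 |
| 0.7 | 0.33 | 0.51 |
| 0.9 | 0.17 | 0.23 |

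**Both required, one named sEMG variable.** Alpha stays at or below .05. If each test has 80% power, joint power is 0.80 × 0.80 = 0.64 if independent and 0.71 at correlation 0.7. With 77% each, as at 32 per group, it is 0.59 to 0.68. The sEMG power is an assumption; the article gives no basis for it. If instead any one of many sEMG variables could satisfy the sEMG half, alpha would not hold for that half: given a true 6MWT effect, the risks in the table return.

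**FDR extended to the primaries.** If one Benjamini-Hochberg family held the 6MWT and 108 sEMG variables, and no sEMG variable truly changed, the first-step threshold is .05/109 = .00046. 6MWT power at 32 per group is then 0.175 (t) or 0.211 (normal) at that threshold, and about 0.22 in simulation of the full procedure. With 27 sEMG variables it is about 0.34 in simulation. Real sEMG effects raise it: with 20 or 40 of 108 independent variables given the same shift of 2.70, 6MWT power is about 0.45 or 0.57.

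**The case against.** **Detail for the analysis plan.** The choice of sEMG summary variable and the FDR family may sit in an analysis plan that is not shown. That is fair for the FDR family and for signal-processing detail. It does not cover what the article itself fixes: two co-primary domains, a passage naming only one as the primary endpoint, and a sample size for one test. What the primary endpoint is and when the trial succeeds are protocol content.

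**The count and the 99.6%.** A reader might infer that there are at least 108 primary tests and a near-certain false positive. The documents do not support that. Full crossing is not stated. Root mean square and averaged EMG are both assigned to activation intensity, so strong correlation is likely, and the lower rows of the table are the more plausible ones. Those rows are still above .05.

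**The FDR clause.** A reader might infer that FDR sinks the 6MWT test to about 17% power. In Statistical Analysis the clause closes the sentence on secondary and other variables, while the primaries are in the preceding paragraph. On that reading the 6MWT is tested at .05, as sized. The 17 to 22% also needs no true sEMG effect, contrary to the trial's hypothesis. Only the word *throughout* leaves the matter open.

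**The mixed model.** The power figures use the plan's SD of 80 m and no baseline gain. For the group-by-time contrast at 32 per group, an assumed baseline-to-follow-up correlation of 0.5 reproduces 76%, 0.7 gives 93% and 0.8 gives 99%. The article states no correlation. This may help the 6MWT; it does not supply an sEMG endpoint or a success rule.

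**Disclosure.** The article says openly why sEMG could not be sized. That is candid, but it argues for a lower tier for sEMG and does not justify an unsized co-primary.

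**Conclusion.** The concern stands in a limited form. sEMG is declared co-primary without a testable endpoint or a both-or-either rule, and the stated alpha of .05 and power of 80% describe one 6MWT test, not the co-primary claim.

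It would go too far to say that both the error rate and the power fail. No single rule produces that from multiplicity: the *either* rule inflates alpha without reducing the chance of a positive result, and the *both* rule with one named variable keeps alpha and loses power. They are undefined until a rule is fixed, and under unadjusted testing one of them departs from what is stated.

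The size is 0.0975 at the least for two independent tests under the *either* rule. It is 0.17 to 0.75 (27 variables) or 0.23 to 0.996 (108) among sEMG variables alone, over assumed correlations 0.9 to 0. Under the *both* rule joint power is about 0.64, assuming 80% each and independence.

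Two neighbouring faults are separate. The formula gives 35 per group, not 32, so power at 32 evaluable is about 76 to 77% for reasons unrelated to multiplicity. IKMT is exploratory in the Abstract ("Exploratory outcome measures include isokinetic strength testing of the core muscle groups and kinematic analysis") but listed as secondary in the Overview of Secondary Outcome Measures ("isokinetic muscle strength test (IKMT) of the core muscle group"). That is a labelling inconsistency and does not bear on the primary claim.

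**What to change.** Amend the protocol and registry entry, with a date, before analysis. Either option works:

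- **(a)** Make the 6MWT the single primary endpoint at two-sided .05, as sized and as one part of the Discussion already says. Name one sEMG variable (muscle, manoeuvre, parameter, direction of benefit) as key secondary, tested only if the 6MWT is significant.
- **(b)** Keep sEMG co-primary as one such named variable, state that both are required, and state that the 80% power applies to the 6MWT only.

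In both cases, put the remaining sEMG variables in an exploratory family with FDR inside it, and state that the FDR clause does not apply to the 6MWT test. Align the Abstract, the outcome sections and the Discussion. At the same time, correct the sample-size arithmetic and give IKMT one tier.

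The cost is wording, plus the loss of primary status for most sEMG results, which suits a measure that could not be sized. The Results section reports 23 of 76 participants enrolled and analysis planned for January 2027, so the choice can still be made before the results are known. Made after unblinding, it would be post hoc.

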**Figure 3. F3:**
[figure not shown]
Electrode placement for surface electromyography assessment of respiratory muscles. Electrodes were placed on the sternocleidomastoid, trapezius, intercostal muscles, diaphragm, rectus abdominis, external oblique, internal oblique, transversus abdominis, and multifidus muscles according to the SENIAM (Surface Electromyography for the Non-Invasive Assessment of Muscles) recommendations.

#### 6MWT

6MWT is a widely used method for evaluating exercise capacity in patients with respiratory disorders and for assessing the efficacy of clinical interventions. Previous studies [48,49] have demonstrated that the 6MWT serves as a valid and reliable measure of functional capacity and health-related quality of life in patients with COPD, while also providing an indicator of disease severity. Based on previous findings [37,38], the MCID for 6MWT ranges from 30 to 54 m, and the baseline SD is between 70 and 90 m. This study will use a 6MWT data acquisition system in combination with a dynamic vital signs monitor, CB200 (Contec), for testing. Participants will be instructed to walk back and forth along a 30-meter flat corridor at their maximum tolerable speed for six minutes. Distance markers will be placed every 5 meters to aid measurement. The recording device will capture the total walking distance as well as heart rate and oxygen saturation before and after the test. The 6MWT outcome will serve as a primary indicator of intervention efficacy, assessed in week 0 and week 13.

### Secondary Outcome Measures

#### Overview

The secondary outcomes of this trial include PFT, St. George’s Respiratory Questionnaire (SGRQ) and isokinetic muscle strength test (IKMT) of the core muscle group.

#### PFT

PFT is widely recognized as the gold standard for the diagnosis and clinical efficacy assessment of COPD. A previous study [50] has demonstrated that PFT not only provides precise measurements of multiple pulmonary function parameters at rest but also serves as a reliable predictor of long-term prognosis. In this study, PFT will be performed by experienced respiratory technicians in the Pulmonary Function Laboratory of Shanghai Changhai Hospital using a Masterscreen-PFT system (Jaeger), strictly following the standardized procedures recommended by the 2021 ATS/ERS guidelines [51]. Before testing, participants will inhale salbutamol, and measurements will be conducted 25 minutes postinhalation [52]. During testing, participants will be instructed to perform forced exhalations lasting at least six seconds per maneuver, followed by brief rest intervals, and to repeat the maneuver until at least three acceptable measurements are obtained. Recorded parameters include FVC, FEV1, the FEV1-to-FVC ratio (FEV1/FVC), percentage of predicted FEV1 (forced expiratory volume in one second percentage predicted), percentage of predicted FVC (forced vital capacity percentage predicted), and the percentage value of FEV1/FVC (FEV1/forced vital capacity percentage). PFT assessments will be performed in week 1 and week 13.

#### SGRQ

SGRQ is a simple, effective self-administered instrument widely used for the assessment of respiratory diseases, including chronic bronchitis and COPD [53]. A previous study [54] has demonstrated a strong correlation between SGRQ scores and changes in COPD severity, making it a valuable tool for evaluating disease status and predicting prognosis. The total score ranges from 0 to 100, with higher scores indicating poorer health-related quality of life. Based on prior evidence [55,56], a reduction of at least four points in the total score was considered the MCID. In this trial, the SGRQ will be administered at baseline and post intervention. Paper-based questionnaires will be collected and analyzed in a standardized manner to generate total scores and three component scores—symptoms, activity, and impacts. Assessments will be conducted by trained research team members in week 0 and week 13.

